### Participant inclusion and exclusion criteria

All participants will be aged 18–65 years, men/women [24], more than one year after SCI, with body mass index (BMI) ≤ 30 kg/m^2^ [23]. Participants with traumatic motor complete or incomplete C5-L2 level of injury, the American Spinal Injury Association (ASIA) Impairment Scale (AIS) classification A, B, or C will be considered for the trial. Participants with any of the following pre-existing medical conditions will be excluded: cardiovascular disease; uncontrolled type II diabetes mellitus; uncontrolled hypertension; insulin dependence; pressures sores stage 3 or greater; hematocrit > 50%; symptomatic urinary tract infection; or participants with neck of femur or total body osteoporosis (T-score ≤ − 2.5 according to the World Health Organization guidelines.) [26].

## Interventions

### Resistance training

A recent video publication provided full details on the NMES-RT protocol [27]. Briefly, NMES will be applied to the knee extensor muscles via surface electrodes to induce concentric-eccentric actions. Two 8 × 10 cm^2^ adhesive carbon electrodes will be placed on the skin over the knee extensor muscle group. Current from the stimulator will be manually increased in 5-s intervals to evoke full knee extension against gravity followed by gradual reduction of current to induce eccentric action during relaxation. Training will be performed twice-weekly for 12 weeks. Each training session will consist of four sets of 10 repetitions of NMES with 30 Hz, 450 μs pulses, and a current sufficient to evoke full knee extension [28–30]. The first week of the RT will be conducted with no ankle weights to ensure that the knee extensor muscles can extend the weight of the lower leg against gravity [3, 23]. Once full knee extension is achieved in a sitting position, an increment of 2 lbs will be used on a weekly basis with the criteria that full knee extension should be achieved before further increases in load [21–24, 31].

### Passive range of motion for control

A member of the research team supports the leg proximal to the ankle joints and moves it from 90° knee flexion close to full knee extension. The leg will be maintained up for 5 s and returned down for 5 s. The passive movements will be repeated in the same fashion described in RT protocol: 10 reps for the right leg followed by 10 reps for the left leg for a total of four sets of 10 reps.

### Functional electrical stimulation-lower extremity cycling

A recent video publication provided full details on the FES-LEC protocol [27]. Briefly, rides will be performed with each individual using conductive adhesive gel electrodes [19, 32]. Rectangular adhesive electrodes are placed on the skin of the knee extensor, hamstrings, and gluteus maximus muscle groups. Pulse frequency will be set at 33.3 Hz, pulse duration at 350 μs, and resistance will be adjusted every 10 min to maintain a speed of 40–45 rpm (RPM). Table 3 highlights the progression of resistance in 0.5-Nm increments per 10-min stage over the course of 12 weeks. The progression in resistance was customized based on the individual’s performance riding the FES-LEC over 12 weeks. Initially, the servo-motor of the bike is permitted to assist during the warm-up phase (5 min) and during training to reduce muscle spasms. Participants are then allowed 2–3 min of rest between each 10-min stage. Time to maximum (100%) current amplitude, power, and distance covered will be recorded at the end of each stage to determine whether these parameters improved in both groups (NMES + FES versus control). The fatigue threshold will be set at 18 RPM; if RPM falls below 18 RPM, the bike will automatically shift from active to passive cycling (cool-down). During the 3-min cool-down period, participants will be passively cycled with no electrical stimulation. The cool-down period will then be followed by 5 min of recovery, during which the participant will be still connected to the bike but in a complete resting position. Heart rate will be monitored every 30 s and blood pressure every 2 min.

**Table 3 Tab3:** Progression of resistance in 0.5-Nm increments per 10-min stage

	Visit 1			Visit 2			Comment
	Stage 1 (10 min)	Stage 2 (10 min)	Stage 3 (10 min)	Stage 1 (10 min)	Stage 2 (10 min)	Stage 3 (10 min)	
Week 1	1 Nm	1.5 Nm	2.0	1 Nm	1.5	2.0	If completing the 2 visits without the motor turned on, paradigm will change in week 2
Week 2	1.5 Nm	2.0	2.5	1.5 Nm	2.0	2.5	If the motor tuned on, the same paradigm will be maintained in week 3
Week 3	1.5 Nm	2.0	2.5	1.5 Nm	2.0	2.5	If completing the 2 visits without the motor turned on, paradigm will change in week 4
Week 4	2 Nm	2.5	3.0	2 Nm	2.5	3.0	And so on till week 12

The use of NMES-RT or FES-LEC may result in the following potential harms and complications:
Light-headedness, shortness of breath, and altered heart rate and blood pressure leading to autonomic dysreflexia. Muscle soreness of the neck, upper back, shoulders, arms, and hands;Fracture of the exercising bones;Autonomic dysreflexia (slow heart rate, high blood pressure, headache flushing, and sweating) which may be life-threatening;Skin irritations or pressure injuries from shear stress that may lead to breaking the skin;Fainting or heart attacks.

Blood pressure will be continuously monitored during exercising sessions to ensure there are no signs of orthostatic hypotension or autonomic dysreflexia; participants will be regularly checked for any changes in their physical status or health compared to their initial admission in the study and the SCI provider will be notified immediately. Before admission to the study, participants will undergo DXA scans (see below) to ensure adequate bone health—especially at the hip joints (T-scores < − 2.5 SD), distal femur, and proximal tibia (bone mineral density should be > 0.6 g/cm^2^)—to reduce the likelihood of fracture during exercising. The skin will be checked continuously on a regular basis before and after removal of the electrodes to ensure there is no redness or tendency to develop skin irritations and/or pressure injuries.

Other unanticipated adverse events will be monitored throughout the study via exams, vital signs, laboratory tests, review of medical charts, and verbal concerns voiced by the participant or an associated caregiver. Finally, data safety monitoring board of independent research investigators will annually review the study-related adverse events, adequacy of individuals’ compliance, and adherence to the protocol.

## Measurements

### Metabolic studies

#### Dietary records and basal metabolic rate

Each participant will follow a standard diet pattern during the entire period of the study (45% carbohydrate, 35% fat, and 25% protein) to balance dietary habits between both groups [23]. All participants will be asked to complete a three-day food record monitoring their energy intake each week. Previous work showed that three-day records are equivalent to five-day records in reporting caloric intake and percentage macronutrients [28]. Caloric needs will be determined using individuals measured BMR. The diaries will be evaluated weekly by the dietitian and monthly feedback will be provided via phone interview or secure email communication to ensure adherence to the recommended dietary plan throughout the study. All participants will meet with the dietitian three times: at baseline, P1, and P2.

After an overnight fast for 10–12 h, participants will be kept in a dark room for 20–30 min to attain a resting state, during which BMR will be measured by using a canopy that covers the whole head and a portable COSMED K4b2 (COSMED USA, Chicago, IL, USA). BMR and respiratory exchange ratio (RER) will be recorded by indirect calorimetry [3, 33, 34].

#### Serum total, free testosterone, IGF, FFA

Total testosterone measurements will be performed by radioimmunoassay after sample extraction and column chromatography. The interassay coefficient of variation (CV) is 12.5% or less for all quality control samples analyzed. Free testosterone concentrations will be calculated by measuring sex hormone binding globulin (SHBG) and albumin (http://www.issam.ch/freetesto.htm) [35]. Plasma IGF-I and IGFBP-3 concentrations will be measured by immunoluminometric assay (Quest Diagnostics, Madison, NJ, USA) and RIA (Diagnostics Systems Laboratories Inc., Webster, TX, USA), respectively. A total of 10 mL of blood will be collected from the indwelling venous catheter and lipid profile (HDL-C, LDL-C, total cholesterol, and TG) will be determined using standard analyses procedures.

#### Inflammatory biomarkers

Before starting the IVGTT and following a 12-h fast, blood will be collected from the indwelling venous catheter and CRP, IL-6, TNF-α, and FFA will be determined by the VCU-CRC using available enzyme-linked immunosorbent assay (ELISA) assay kits [36, 37].

#### Intravenous glucose tolerance test: primary outcome variables

An IVGTT will be used to determine insulin sensitivity and glucose effectiveness [38, 39]. Each individual will undergo an IVGTT before (baseline) and 12 weeks after interventions (Post 1 and Post 2). After a 10–12-h fast, an indwelling catheter with an intravenous saline drip (0.9% NaCl) will be placed; after 20 min of glucose injection, a bolus of insulin (0.02 U/kg) will be injected to determine insulin sensitivity. Plasma glucose will be measured by the Autoanalyzer glucose oxidase method and plasma insulin concentrations will be determined by commercial radioimmunoassay. The S_I_ (glucose disposal rate per unit of secreted insulin per unit time, i.e. insulin sensitivity) and S_G_ (glucose mediated glucose disposal rate) will be calculated from a least-squares fitting of the temporal pattern of glucose and insulin throughout the IVGTT using the MINMOD program [38, 39].

#### Oxygen uptake and energy expenditure during FES-LEC

One week before intervention (week 1), post-interventions 1 (week 14) and 2 (week 27), peak oxygen uptake (VO_2_) will be measured using a COSMED K4b2 (COSMED USA, Chicago, IL, USA) portable metabolic unit [19]. After calibration, individuals will be asked to place the mask on their face to monitor oxygen (VO_2_) and carbon dioxide (VCO_2_) production. A 3-min resting phase allows the participant to get used to breathing with the mask on while they are attached to the RT-300 bike. After the resting phase, VO_2_ will be measured during the 3-min warm-up phase, the resistance of the bike will be gradually increased by 2 Nm every 2 min until fatigue. During testing, the servo-motor will be tuned off and the cool-down phase will then be followed by the recovery phase [19].

VO_2_ and VCO_2_ will be monitored throughout exercise to determine total energy expenditure using the Weir equation. Five minutes of recovery will be recorded to determine the efficacy of each intervention on energy expenditure and substrate utilization. Heart rate (via polar HR monitor) will be recorded every 30 s and blood pressure (COSMED 740) will be recorded before, every 2 min during cycling, and for another 5 min after cycling to ensure full recovery to baseline.

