Functional electrical stimulation (FES) is a form of neuromuscular electrical stimulation (NMES) which provides stimulation of selected muscles in a coordinated manner resulting in a functional pattern such as walking, cycling, or rowing. This is contrary to surface NMES which is used for a single or multiple muscle groups to exercise or to move specific joint, but without the intention of producing a functional or coordinated movement [17]. FES-lower extremity cycling (LEC) is limited by the low exercise intensity, low peak oxygen uptake (0.4 L/min), and rapid muscle fatigue, which renders FES-LEC training a suboptimal modality to increase gain in lean mass and improve metabolic health after SCI [18, 19]. This may result from a mismatch when converting metabolic energy into mechanical energy.

Neuromuscular electrical stimulation (NMES) has been used to evoke exercise-induced resistance training (RT) using regular ankle weights in individuals with chronic SCI [20–24]. Several research groups demonstrated the efficacy of this approach in evoking robust muscle hypertrophy [21, 24, 25]. Dudley et al. showed that eight weeks of twice-weekly NMES RT reverted knee extensor muscle size to 75% of original size at six weeks after SCI [21]. Follow-up studies reported a 35–39% increase in muscle hypertrophy and 33% fatigue resistance of the trained knee extensors [22, 23]. Gorgey et al. noted that 12 weeks of twice-weekly NMES RT elicited an increase in skeletal muscle size of > 35%, decreased IMF and VAT by 25%, and increased insulin sensitivity and insulin growth factor-1 (IGF-1) by 25% [23]. Finally, Ryan et al. noted improvement in mitochondrial capacity by 25% following 16 weeks of twice-weekly evoked NMES RT in persons with chronic complete SCI [24]. A recent study demonstrated that 16 weeks of NMES-RT combined with testosterone replacement therapy (TRT) resulted in a 43% muscle hypertrophy of the knee extensor and 21% increase in thigh muscle cross-sectional area (CSA) accompanied with 14–17% increase in daily basal metabolic rate (BMR) compared to TRT only. [25]

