The objectives of the current trial are to determine the impact of evoking skeletal muscle hypertrophy using surface NMES and ankle weights before conducting FES-LEC on oxygen uptake, insulin sensitivity, and glucose effectiveness (primary endpoint variables) compared to those who undergo passive movement and FES training only. The primary question is: does evoking skeletal muscle hypertrophy lead to improvement in metabolic health benefits as outlined in Fig. 1? This prospective randomized clinical trial will also shed light on the mechanism and signaling pathways responsible for evoking hypertrophy, enhancing energy, and substrate utilization as well as improving glucose metabolism.

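### Substrate utilization is to be judged from 5 min of recovery after a ride to fatigue, a window in which RER cannot be interpreted as fuel use

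*Protocol article*

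**What the plan says.** The peak VO2 test described under Oxygen uptake and energy expenditure during FES-LEC is incremental: "the resistance of the bike will be gradually increased by 2 Nm every 2 min until fatigue". The phases then run in sequence: "the servo-motor will be tuned off and the cool-down phase will then be followed by the recovery phase". Two uses of the gas-exchange data are stated. During the ride, VO2 and VCO2 "will be monitored throughout exercise to determine total energy expenditure using the Weir equation". After it, "Five minutes of recovery will be recorded to determine the efficacy of each intervention on energy expenditure and substrate utilization". The section describes no constant-load stage, no RER limit and no allowance for CO2 that does not come from oxidation.

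Substrate utilization also appears in the objectives at the end of the Background, where the trial is to inform on mechanisms for "enhancing energy, and substrate utilization as well as improving glucose metabolism".

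A separate resting measurement is made under Dietary records and basal metabolic rate, after a 10–12 h fast and 20–30 min in a dark room: "BMR and respiratory exchange ratio (RER) will be recorded by indirect calorimetry". The article does not link this measurement to substrate utilization.

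**The concern.** Indirect calorimetry gives the fuel mix only when the CO2 leaving at the mouth equals the CO2 produced by oxidation. That needs steady gas exchange. In the minutes after exercise to fatigue, buffering of acid and hyperventilation add CO2 that no fuel produced, which raises RER. Later, refilling of CO2 stores holds CO2 back, which lowers it. RER in this window depends on how hard the participant worked and how long ago the work stopped.

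Randomization does not remove the problem, because effort lies on the path from treatment to measurement. The Abstract's Discussion anticipates better workloads from adding NMES-RT to FES-LEC, and the Background hypothesizes larger gains in aerobic fitness. If those expectations are met, the arms enter recovery from different efforts. A group-by-time comparison could then present a by-product of the test as a change in fuel use.

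**Working it through.** The article gives no figure on this point, so there is nothing to reproduce. The check asks how far calculated fuel use moves when CO2 output departs from oxidative CO2.

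**Inputs**
- VO2 of 0.4 L/min: the peak figure for FES-LEC in the Background. Recovery VO2 should be lower, so 0.25 L/min is added as an assumption.
- True tissue respiratory quotient (RQ): assumed 0.85, with 0.80 to 0.95 for sensitivity.
- Measured RER: assumed, 0.70 to 1.20.
- Protein oxidation is ignored.
- Weir coefficients: assumed 3.941 and 1.106. The article names the equation without them.

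**Formulas.** Glucose + 6 O2 gives 6 CO2 (RQ 1.000). Palmitate + 23 O2 gives 16 CO2 (RQ 16/23 = 0.696). At 22.4 L/mol:
- glucose uses 6 × 22.4/180.16 = 0.746 L O2 per g and yields the same volume of CO2;
- palmitate uses 23 × 22.4/256.42 = 2.009 L O2 per g and yields 16 × 22.4/256.42 = 1.398 L CO2.

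Solving the two balances:
- fat (g/min) = (VO2 − VCO2)/(2.009 − 1.398) = 1.635 × VO2 × (1 − RER)
- carbohydrate (g/min) = (VO2 − 2.009 × fat)/0.746
- Weir energy expenditure (kcal/min) = 3.941 × VO2 + 1.106 × VCO2

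**Results when true RQ is 0.85** (carbohydrate / fat, g/min)

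| Measured RER | VO2 0.4 L/min | VO2 0.25 L/min | Error in Weir expenditure |
|---|---|---|---|
| 0.70 | 0.008 / 0.196 | 0.005 / 0.123 | −3.4% |
| 0.85 (true) | 0.272 / 0.098 | 0.170 / 0.061 | 0 |
| 0.90 | 0.360 / 0.065 | 0.225 / 0.041 | +1.1% |
| 1.00 | 0.536 / 0 | 0.335 / 0 | +3.4% |
| 1.10 | 0.712 / −0.065 | 0.445 / −0.041 | +5.7% |
| 1.20 | 0.889 / −0.131 | 0.555 / −0.082 | +7.9% |

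Calculated fat is negative whenever RER exceeds 1.0, and calculated carbohydrate is negative whenever it is below 0.696.

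**Relative error.** Both fuel terms are proportional to VO2, so VO2 cancels. From RER 0.9 to 1.2, apparent carbohydrate use rises by 0.889/0.360 = 2.47 at 0.4 L/min and 0.555/0.225 = 2.47 at 0.25 L/min. The conventional form, carbohydrate = VO2 × (4.55 × RER − 3.21), gives 2.25/0.885 = 2.54. Either way it is about 2.5-fold with no change in fuel.

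**CO2 needed.** Non-oxidative CO2 that brings calculated fat to zero at 0.4 L/min is 400 × (1 − RQ) mL/min: 80, 60, 40 and 20 mL/min for true RQ 0.80, 0.85, 0.90 and 0.95. These are 25%, 18%, 11% and 5% of oxidative VCO2, so modest departures are enough.

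**The case against.** The strongest reply is that this is a condensed article. It gives no substrate equation, no g/min outcome and no rule for handling recovery gas exchange, and a fuller protocol may do so. That stands against any statement that the reported fat and carbohydrate values will be wrong. It does not remove the point, because the article itself names the window and the inference to be drawn from it.

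Four stronger readings are tempting, and the article does not support them.
- A reader might infer that substrate use is also to be taken from the ride. The text assigns ride data only to energy expenditure, which the Weir column shows is fairly robust.
- A reader might infer a conflict with a hypothesis of greater fat use. The hypotheses in the Background contain none. The nearest text is a general remark in the Discussion about intramuscular fat as fuel during FES-LEC.
- A reader might infer that the NMES + FES arm will be distorted more. Both arms ride to fatigue, a cool-down comes first, and the two CO2 effects oppose each other. No figure gives the sign, the size or the difference between arms. A differential bias is possible, not shown.
- A reader might take the g/min values as recovery values. The 0.4 L/min is a peak figure; only the ratios carry over.

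It is also fair to say that little rests on this outcome. The primary variables are VO2, insulin sensitivity and glucose effectiveness, and substrate utilization is not named in the Statistical analyses section.

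**Conclusion.** The point holds for the recovery window only. RER over 5 min of recovery after a ride to fatigue and a cool-down cannot be interpreted as substrate use. It may be biased up or down, and possibly by different amounts in the two arms. Under assumed RERs the distortion is large for fuel use (about 2.5-fold for carbohydrate between 0.9 and 1.2, negative fat above 1.0). It is small for Weir energy expenditure (−3.4% to +7.9% over RER 0.70 to 1.20 at a true RQ of 0.85). The size and direction in this trial are unknown, because the article gives no RER data. Severity is low: a secondary mechanistic outcome is affected and no primary conclusion changes.

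**What to change.** Under Oxygen uptake and energy expenditure during FES-LEC, remove substrate utilization from the purpose of the recovery recording and keep that recording for VO2 and energy expenditure. Under Dietary records and basal metabolic rate, name the fasting resting RER as the source for substrate utilization at baseline, P1 and P2, and state that it describes resting fuel use, not fuel use during exercise.

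The change is one of wording. Resting RER is already recorded, and Table 2 schedules the metabolic variables at all three assessments. The section on BMR does not itself list the visits, so the schedule should be confirmed there.

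The cost is a narrower claim: the trial could no longer speak about substrate use in response to FES cycling. Keeping that claim would need steady-state exercise data, which the article does not describe and which could not be added for the 21 participants that Table 2 shows as already completed.

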### Body composition

#### BMI and anthropometrics

Each participant will be asked to empty their bladder and then will propel onto a wheelchair weighing scale to evaluate weight in kilograms. The wheelchair will be measured separately and the difference will be taken for the final weight. The height of each participant will be determined with the individual on his/her right side in the supine position. Two smooth wooden boards will be placed at the participant’s head and heels and the distance between them corresponds to the height in nearest centimeter. The BMI (kg/m^2^) will be calculated as weight (kg)/height (m^2^). Anthropometrics will be determined in duplicate by identifying the narrowest region of the trunk from sitting and lying positions. After normal expiration, a tape measure will be used around the participant’s trunk to measure waist circumference (WC) [33, 40, 41].

#### Dual energy X-ray absorptiometry (DXA)

DXA will be used to measure body composition in SCI individuals, specifically regional and total fat mass (FM) and fat-free mass (FFM). Total body and regional (lumbar spine, proximal femur, and forearm) DXA scans will be performed using a GE Lunar iDXA (Lunar Inc., Madison, WI, USA) bone densitometer at the Hunter Holmes VAMC hospital. All scans will be performed and analyzed using Lunar software version 10.5. After scanning, total and regional % FM and FFM will be determined using DXA software. The longitudinal precision of total and regional body composition using DXA was recently determined in persons with SCI [42].

#### Magnetic resonance imaging (MRI)

Skeletal muscle CSAs will be determined before (baseline) and twice after 12-week interventions (post-interventions 1 and 2) using a 1.5-Tesla GE magnet. Transaxial images, 0.8 cm thick and 1.6 cm apart, will be taken from the hip joint to the knee joint (thigh) and from knee to the ankle (leg) using the whole-body coil [19, 20, 43–46]. T1-weighted imaging will be performed using a fast spin-echo sequence to capture visceral fat images. To measure visceral adipose tissue (VAT) and subcutaneous adipose tissue (SAT), transverse slices (0.8 cm thickness) are acquired every 0.4-cm gap from the xyphoid process to the femoral heads. Images will be acquired in a series of two stacks with L4-L5 used as a separating point. Participants will be asked to take a deep breath in and hold their breath for 10–15 s to reduce the respiratory-motion artifact associated with MRI for the abdominal region [19, 29, 47].

